## Abstract

**Background:**

Reports suggest that > 90% of the cases go undetected in low- and middle-income countries (LMICs) leading to a huge treatment gap. Evidence shows that task-sharing interventions such as training HWs, screening led to improved detection of depression at the primary level. In this regard, the World Health Organization (WHO) developed the mhGAP-IG to aid non-specialist HWs to detect and manage common mental health disorders such as depression to bridge the gap. The present study aims to design and test the effectiveness of a digital mental health intervention designed by contextualizing e-mhGAP in improving the detection and management of depression at the primary care level.

**Methods:**

Formative phase will involve qualitative interviews, literature review aimed at co-developing a mobile application with the district mental health program. This will be followed by a cRCT. The trial will be conducted in eight PHCs, located in Tumkur district, Karnataka, and Wardha district, Maharashtra. Randomisation will be done at the PHC level. We plan to enrol non-specialist HWs working in these PHCs and a sample of 2400 adults who are availing the PHC services. Intervention PHC will receive training for HWs and a mobile application. Control PHCs will follow usual care. Both the groups will be encouraged to identify, manage, and follow-up people with mild depression. Study tools include PHQ-2, PHQ-9, acceptability of intervention measure, and Eq. 5D5L instrument. Change in the detection rates of depression between intervention and control arms will be the primary outcome. Cost effectiveness analysis will be done.

**Discussion:**

This trial advocates for integrating mental health services into primary healthcare, which aligns with the Comprehensive Mental Health action plan that seeks to enhance the capacity of non-specialist HWs in mental healthcare delivery. Co-development with the district mental health program, features of app such as offline functionality, multimedia visuals, and follow-up tracking are some of the strengths. If this intervention is found effective, then it could significantly impact the treatment gap for depression by integrating mental health within the ambit of primary care model across India.

**Trial registration:**

Prospectively registered with the Clinical Trials Registry of India on 23/04/2024 (Reference number- CTRI/2024/04/066142).

**Supplementary Information:**

The online version contains supplementary material available at https://doi.org/10.1186/s12889-026-28263-7.

## Background

Globally 280 million people were suffering from depressive disorders, and it accounted for the largest proportion of mental disorder Disability Adjusted Life Years (DALYs) of 37.3% in 2019 [1]. In India, depression affected over 5% of the adult population [2]. Despite availability of effective interventions, the vast majority of people with depression do not receive any care [3, 4]. Untreated depression is a leading cause of disability and suicide [5]. Compared to general population, people with depression have a 40–60% higher chance of premature mortality [6–8]. Yet, detection rates of depression in the primary care settings is extremely low and reports suggest that > 90% of the cases go undetected in low- and middle-income countries (LMICs) leading to a huge treatment gap [9–10].

India provides health services including mental healthcare through a three-tier public health system [11]. Through the National Mental Health Program (NMHP), India envisages providing universal access to mental healthcare [12]. The District Mental Health Programme (DMHP) under NMHP focuses on delivering mental healthcare in a decentralized manner. In many states, DMHP has launched specific programs to integrate mental healthcare into public health facilities [13]. However, the success of these programs are limited to district level [14]. 

One of the barriers to integrating mental healthcare into primary care includes shortage of human resources [3, 6]. India faces hurdles in delivering mental healthcare due to a shortage and unequal distribution of trained mental health professionals between urban and rural areas [3]. Low mental health literacy, persisting stigma and discrimination in rural India, further exacerbates this issue [15]. Therefore, task-sharing, a process of training non-specialist health workers (HWs) to contribute to detecting, diagnosing, and treating various mental disorders, is a promising strategy [16]. Evidence shows that interventions such as training HWs, screening, feedback, and standard guidelines led to improved detection of depression at the primary level [17]. Increasingly, such task sharing strategies targeting primary-level HWs are being emphasized by the DMHP [14]. 

A review of psychosocial interventions for common mental disorders by non-specialist HWs in LMICs demonstrated the effectiveness of these interventions. Studies from India targeting non-specialist HCWs to manage mental disorders have been encouraging [18–21]. Some demonstrated the effectiveness of task-sharing interventions in the management of depression [22]. Hence, task-sharing is a promising approach for overcoming workforce shortages and strengthen detection and management of common mental disorders [16, 23]. 

The framework proposed to illustrate the role of technology in supporting HWs in delivering evidence-based mental healthcare includes competency-based training; digital interventions to support delivery of mental health care; and digital strategies to facilitate supervision and promote retention [23, 24]. However, training alone is insufficient in improving detection rates of depression [5]. Enhancing HWs’ training using validated digital tools for patient screening can be more effective. This framework helps in understanding the potential of digital interventions in maximizing skills of HWs in dealing with people with depression. Mobile health interventions have already shown potential in community settings—notably, the MITHRA application, which provided depression screening and brief interventions for women in rural India through self-help groups [25, 26]. 

The World Health Organization (WHO) developed the Mental Health Gap Action Programme Intervention Guide (mhGAP-IG), for primary-level non-specialist HWs wherein evidence-based algorithms aid HWs in managing mental health conditions, while the training packages and implementation tools facilitate integration with the health system [27]. mhGAP-IG has been implemented in over 100 countries [22, 28–30]. WHO released a smartphone-based e-mhGAP application in 2017 [31]. The e-mhGAP faced challenges like limited patient-specific interventions, offline functionality, and language support [32, 33]. While using mobile applications, diagnostic suggestions, follow-up reminders, offline access have been reported to be beneficial by HWs, but barriers included internet reliance, and distraction in the communication between patients and HWs [32]. A feasibility cluster randomized controlled trial (cRCT) reported increased usability of the application, higher satisfaction, and cost-effectiveness [31]. An Indian study found training completion rate for a digital program on depression to be satisfactory. However, challenges such as mobile network issues, difficulty navigating the content, and device hardware problems highlighted the need for augmented digital infrastructure [34]. 

### Rationale

There is a lack of systematic research on using e-mhGAP for managing depression in India [30]. The present study is designed to address challenges and limitations based on the evidence originating from LMICs. For instance, the mhGAP is only available in Marathi language [35]. For successful implementation, the intervention must be contextually adapted, available in regional languages and provide support for trainees [33, 36]. Therefore, this study aims to design a digital intervention by contextualizing e-mhGAP and test it in rural Karnataka and Maharashtra. Additionally, we seek to improve the psychological intervention of the depression module by incorporating multimedia to help HWs deliver mental healthcare confidently. The study’s goal is to integrate mental health services into primary care through a technology-driven approach which aligns with that of NMHP. In summary, task-sharing and the use of a novel mobile application in rural India hold promise in reducing the prevailing treatment gap for depression.

## Methods

### Objectives

Primary:

To co-develop a mobile application based on e-mhGAP IG for the detection and management of persons with mild depression by HWs.To evaluate its effectiveness of this digital mental health intervention in the detection and management of persons with mild depression by HWs, compared to usual care in rural PHCs in two states of India.

Secondary:

3.To determine the acceptability and feasibility of this digital mental health intervention among HW.4.To determine the cost-effectiveness of digital mental health intervention in improving the detection and management of mild depression by HWs.

### Study design

This will be an equal-arm parallel-group cRCT across two sites (Tumkur and Wardha). The cluster randomized design was chosen to ensure balance between methodological rigour and real-world feasibility focussed on conducting the research under practical primary care conditions relevant for programmatic decision making.

### Study setting

The trial will be conducted in eight PHCs, located in Tumkur district, Karnataka, and Wardha district, Maharashtra. Tumkur district has ten administrative sub-divisions and 150 PHCs, while Wardha district has eight sub-divisions and 33 PHCs. The PHCs are located between 30 and 100 km from the study sites. PHCs will be ranked based on the criteria given in Table 1. The top 20 ranked PHCs will be listed in descending order, and four PHCs will be randomly selected from each site.

**Table 1 Tab1:** Criteria for selection of PHCs

PHC selection criteria	Ranking based on
*1. Distance from the study site to the PHC*	Farther less score
*2. Population catered by the PHC*	≥ 30,000 higher score
*3. Number of HWs working in the PHC*	≥ 10 higher score
*4. Monthly footfall of adult patients in the PHC*	≥ 2000 higher score
*5.Ongoing mental health research in the PHC*	Absent more score

### Study participants and eligibility criteria

Non-specialist HWs: As per the Indian Public Health Standards, non-specialist HWs at the level of PHC include staff nurses, auxiliary nurse midwives, community health officers, health assistants, and health educators [37]. HWs belonging to these groups will be recruited based on the inclusion criteria, which include ≥ 12 years of schooling and work experience of ≥ 1 year at the study PHC. Pregnant HWs will be excluded.

Adult participants: This includes adults who visit the study PHCs to avail health services. Those aged between 18 and 60 years, able to understand the local language, and who are likely to stay within the PHC area for the duration of the study will be eligible to participate. Persons with acute medical illness, pre-existing psychiatric conditions, and pregnant or lactating mothers will be excluded.

Stakeholders: Additionally, we will include DMHP administrators, psychiatrists, psychologists, psychiatric social workers, medical officers, technological experts, and HWs from non-study PHCs during the formative phase of the research.

### Interventions

The intervention includes capacity building for HWs, provision of a mobile application containing modules on screening and psychological intervention for managing mild depression (Fig. 1).

**Fig. 1 Fig1:**

Study intervention package

*Co-designing a mobile application*: The existing English e-mhGAP depression module will be culturally adapted to the study setting using a mixed-methods approach. A literature review and technical review of existing m-health applications used in various national health programs will be carried out. To understand the needs, facilitators, and barriers for implementing the digital mental health intervention, we will conduct in-depth interviews (IDI) and focus group discussions (FGDs). We plan to do 30 IDIs and 10 FGDs with all the stakeholders mentioned under study participants. Over the next six months, the research team will conduct 2–3 workshops with all stakeholders and application developers to co-design a mobile application containing modules on screening and managing depression through psychological interventions.

The co-developed application will include initial screening using Patient Health Questionnaire-2 (PHQ-2) [38] and assessment using Patient Health Questionnaire-9 (PHQ-9) [39] tools, psychological intervention modules, handling participant follow-ups, and referrals. We intend to improve the psychological intervention by plugging multi-media content that can aid HWs in counselling participants. One of the salient features will include offline functionality and multi-lingual option. Additionally, tutorials for HWs, user profile management, and action-oriented dashboards will also feature in the application. The software will be developed using the Agile methodology, employing iterative and incremental development cycles to ensure continuous refinement and user-centric improvements. The application will be designed for deployment on both web and Android platforms, utilizing modern open-source frameworks and tools. Development will adhere to the technical standards and guidelines set forth by the Ayushman Bharat Digital Mission (ABDM), ensuring interoperability, data security, and compliance with national digital health infrastructure norms.

Training toolkit for capacity building of HWs: Based the WHO mhGAP-IG [27], a context-specific training toolkit will be prepared which will have a training manual, screening and assessment algorithms, and flipcharts. A panel of mental health experts will face-validate the toolkit. Bilingual experts will translate the toolkit into the local languages (Kannada, Marathi, and Hindi) using a transcultural translation and adaptation (TTA) process [40, 41], which will be reviewed by the research team for accuracy. Back translation will be done to address any discrepancies and finalise the contents.

Capacity building of HWs: HWs in the intervention PHCs will undergo a three-day training led by a psychiatrist and research team using the principles of adult learning. Training topics are presented in Table 2. Short lectures, role-plays, case vignettes discussions, games, group activities, and video demonstrations will be used for training. Each HW will receive a training toolkit. Pre- and post-training assessments of HWs will be conducted using mhGAP knowledge questionnaire. HWs will then receive the mobile application for installing on their smartphone. To enhance HWs’ competencies required for counselling, training will be supplemented by HWs shadowing DMHP psychiatrists at the mental health camp. One refresher session will be held midway through the trial.

**Table 2 Tab2:** Contents of training for capacity building of HWs

Training day	Training topics
*Day 1 (4.5 h)*	Pre-training assessment
	Introduction to common mental health issues Integrating mental health into primary care
	Essentials of mental health care and clinical practice: assessments, management, & practice
	Introduction to depression
	Absent more score
*Day 2 (4.5 h)*	Assessment for (mild/moderate/severe) depression
	Management of depression and non-pharmacological interventions
	Introduction to e-mhGAP and Screening using e-mhGAP
*Day 3 (4.5 h)*	Psychoeducation using e-mhGAP
	Follow-up using e-mhGAP
	Reporting and referrals, assessing suicidal tendency
	Post training assessment and wrap up

### Pilot phase

To assess the feasibility, recruitment rate, and logistical requirements, a pilot will be conducted in two urban PHCs. We plan to include 10–20 HWs working in these PHCs as per the eligibility. HWs at one PHC will receive the intervention package, while HWs at the other PHC will receive a brief sensitisation on mental health issues. The pilot will be conducted over three-months, during which HWs at the intervention PHC will screen 25–50 adults for depression and manage using the mobile application. HWs at the control PHC will screen 25–50 adults for depression and manage with usual care. HWs will counsel participants screened positive for mild depression at the time of identification, and during the 3rd -4th, 7th-8th, and 11th-12th weeks. Recruitment rate, intervention fidelity, and drop-out rate will be measured to guide the main trial protocol.

### Allocation and sequence generation

Randomisation will be done at the PHC level, separately for Tumkur and Wardha districts. Allocation sequence will be independently generated by the study biostatistician. Eight PHCs will be included in the cRCT, with 1:1 allocation ratio.

### Implementation

The project research scientist (PRS) will enrol the study participants after due informed consent. The cRCT will be conducted in four different phases (Fig. 2).

**Fig. 2 Fig2:**
[figure not shown]
Consort flow diagram

Phase I: In this, baseline data collection using outpatient records in all study PHCs will be carried out to determine the PHC footfall, number of adults diagnosed, managed, or referred for mental health conditions over the past six months.

Phase II: PHCs will be randomised and allocated into the intervention arm (*n* = 4) and the control arm (*n* = 4). Subsequently, intervention package will be delivered to HWs in the intervention PHCs. HWs at the control PHCs will receive a one-day sensitisation session on mental health conditions, including brief psychoeducational counselling on depression.

Phase III: Screening, assessment, psychological counselling of adult participants by HWs, and referrals will take place during this phase. In both intervention and control PHCs, adults attending the study PHCs will be enrolled consecutively ss per the eligibility criteria. They will be allotted to each HW depending on the availability of HW in the PHCs for screening, assessment, and management of depression.

Phase IV: In both arms, participants identified with mild depression will receive psychological counselling from HWs and will be followed up as outlined in the pilot phase. Each follow-up counselling session will last 10 min per participant. PRS will give telephonic reminders to participants to reduce dropouts. Screening, assessment, and management of mild depression will be done using application in intervention PHCs and through usual care in control PHCs by the HW.

Validation by PRS: At the time of baseline assessment, the PRS will validate all participants identified with mild depression by HWs. Along with this, PRS will also randomly conduct a validation check PHQ 9 scores in participants identified as normal by HWs. To document changes in PHQ-9 scores, the PRS will administer the PHQ-9 to participants at all follow-up visits. PRS will do a health-related quality of life (HRQoL) assessment at baseline and the last follow-up.

Referral: Participants with PHQ-9 scores ≥ 10 or having suicidal ideation will be referred to the DMHP psychiatrist at the sub-district hospital. The PRS will contact participants telephonically to ensure they receive appropriate care. Throughout the study, the research team will provide weekly supportive supervision to all HWs in both arms to provide feedback and address any issues they may face.

Reimbursements: HWs and adult participants will receive a nominal monetary incentive as reimbursement for their time spent towards the study. The amount will be set at a level that ensures it does not interfere with the voluntariness of participants’ consent.

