### Outcome assessment

Outcomes will be measured at both the PHC and participant levels and have been outlined in Table 3.

**Table 3 Tab3:** Study outcome according to various phases and data sources

Outcome measures	Respondents	Data collection type
*Objective 1*		
* 1. Themes and sub-themes*	DMHP stakeholders, HWs, community members	Qualitative interviews
* 2. Pre and post training scores*	HWs	Study questionnaire
* 3. User validity testing*	DMHP stakeholders, HWs	Observation checklist
*Objective 2*		
* 1. Detection rates of depression*	HWs, adults	Study monitoring forms; application data
* 2. Treatment completion rates*	HWs, adults	Study monitoring forms; application data
* 3. Referral rates*	HWs, adults	Study monitoring forms; application data
* 4. HRQoL scores*	Adults	Study questionnaire
*Objective 3*		
* 1. Acceptability*	HWs	AIM; Qualitative interviews
* 2. Feasibility*	HWs	AIM; Qualitative interviews
* 3. Fidelity*	HWs	AIM; Qualitative interviews, Study monitoring forms
* 4. Theme and sub-themes*	HWs	Qualitative interviews
*Objective 4*		
* 1. Incremental cost effectiveness ratio*	HWs, adults, DMHP stakeholders	Study questionnaire, administrative data, project reports

Acceptability and feasibility: This will be assessed using both quantitative and qualitative methods in the intervention arm. (1) Feasibility: Recruitment and attrition rates will be estimated, and intervention fidelity will be monitored using standard study forms, with any protocol deviations documented. (2) Acceptability: HWs’ acceptance of the intervention will be measured using the Acceptability of Intervention Measure (AIM) instrument. Developed by implementation scientists, the AIM instrument has displayed good psychometric properties [42]. At the end of the trial, FGDs will be conducted with the HWs to understand their perceptions and experiences of using the application.

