### Data collection methods

Qualitative interviews will be conducted using IDI and FGD guides, prepared by the research team. Pre-training and post-training knowledge of HWs will be assessed using mhGAP knowledge questionnaire [44]. 

Screening and assessment of participants will be done using the PHQ-2 and PHQ-9. PHQ-2 has been recommended as a pre-screen prior to administering PHQ-9 items [45]. A score of ≥ 3 requires further assessment with PHQ-9 to determine severity of depression. The PHQ-9, designed for primary care settings, consists of 9 items which measure the frequency of depressive symptoms over the past fortnight. A multicentric Indian study reported PHQ-9 reliable for screening depression by HWs [46]. Table 5 provides the operational definitions of our study.Acceptability and feasibility of the intervention will be assessed using AIM instrument [47]. 

The HRQoL will be measured at baseline and endline by the PRS using EUROQUAL instrument (EQ-5D-5 L), the norms of which are available for the Indian population [48]. 

Detailed costing of every single ingredient will be gathered for doing cost-effectiveness analysis.

**Table 5 Tab5:** Operational definition for PHQ-9 used in the study

Operational definition	PHQ-9 score
*1. Normal*	< 5
*2. Mild depression*	5–9
*3. Moderate depression*	≥ 10
*4. Severe depression*	≥ 15
*5. Recovery*	< 5

The socio-demographic details from participants will be used to generate a unique identification number (UID).

In the intervention arm, screening, assessment, and counselling of participants by HWs, validation by the PRS and follow-up data will be captured in the mobile application. This data will get stored in the application backend which can be downloaded in Microsoft Excel format. In the control arm, screening, assessment, follow-up, and validation data will be captured using a case record form (CRF). This along with the HWs knowledge scores, EQ-5D-5 L scores, AIM scores, and costing data will be collected using Epicollect5 with appropriate quality checks to minimise errors. Respective site PIs will constantly monitor all the data captured through the application and by Epicollect5.

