### Statistical methods

The qualitative data will be audio-recorded and transcribed verbatim. The transcriptions and the field notes from IDIs and FGDs will be manually coded. An inductive-deductive approach will be used to identify key themes and sub-themes. Reporting will be done using the Consolidated Criteria for Reporting Qualitative Studies (COREQ) checklist [49]. 

After checking for normality, continuous data will be expressed using mean (standard deviation) or median (interquartile range). Categorical data will be described using frequency and percentages. The difference in the detection and recovery rates between intervention and control arms, as well as associated risk factors for depression, will be compared using generalised estimating equation (GEE) analysis with a log link and exchangeable correlation structure to adjust for cluster effects. The change in EQ-5D-5 L scores during the follow-up will be compared between two groups using a mixed linear model. A p-value less than 0.05 will be considered significant. Missing data will be handled using multiple imputation methods.

Standard health economic methods will be applied to determine the incremental cost-effectiveness ratio (ICER) based on the costs and outcomes associated with the intervention. Sensitivity analyses will be conducted to test the robustness of the results. All analyses will be carried out using R software. Tree age software will be used to perform cost-effectiveness analyses.

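### The only symptom outcome for management is recovery (PHQ-9 below 5 in people entering at 5–9): it has no stated adjustment for entry score, visit or place in Table 3, and the repeated PHQ-9 scores have no stated analysis

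*Protocol article*

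**What the plan says.** The second primary objective (Objectives) is effectiveness "in the detection and management of persons with mild depression by HWs, compared to usual care in rural PHCs". On the people managed, Implementation (Phase IV) says that in both arms "participants identified with mild depression will receive psychological counselling from HWs and will be followed up as outlined in the pilot phase"; Pilot phase places that counselling "at the time of identification, and during the 3rd -4th, 7th-8th, and 11th-12th weeks".

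Table 5 (Data collection methods) defines mild depression as PHQ-9 5–9 and both normal and recovery as PHQ-9 below 5. It sets no minimum change and names no visit.

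Under Validation by PRS (Implementation), the project research scientist (PRS) validates every participant whom a health worker identifies with mild depression, and then: "To document changes in PHQ-9 scores, the PRS will administer the PHQ-9 to participants at all follow-up visits".

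Outcome assessment says: "Outcomes will be measured at both the PHC and participant levels and have been outlined in Table 3". Under Objective 2, Table 3 lists detection rates, "2. Treatment completion rates", referral rates and health-related quality of life (HRQoL).

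Statistical methods says: "The difference in the detection and recovery rates between intervention and control arms, as well as associated risk factors for depression, will be compared", by generalised estimating equations (GEE) with a log link. Change in EQ-5D-5L gets a mixed linear model. Sample size gives a separate calculation for recovery, 54% against a 20% difference, with 89 patients per arm.

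**The concern.** Three things do not fit together.

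- **The threshold adjoins the entry band.** Recovery begins one point below the lowest entry score, so the same label demands very different improvement depending on where a participant starts. Entry score is then a strong predictor of the outcome, but no adjustment for it is stated.
- **The managed group is formed after randomisation.** Who enters it depends on health-worker detection, which the intervention is designed to alter, and health workers are not blinded. The arms may therefore differ in entry score, and an unadjusted recovery comparison would carry that difference into the apparent effect on management.
- **The outcome list, the data collected and the analysis disagree.** Recovery is sized and analysed but is not in the table said to outline the outcomes. PHQ-9 change is collected for a stated purpose that no listed outcome or analysis serves.

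At stake is whether the management half of the second objective can be read as a treatment effect. The primary outcome, detection, is not affected.

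**Working it through.** **1. The plan's own figure.** Inputs from Sample size: 54% against 74% (20% read as percentage points), 80% power, two-sided 5%. The pooled proportion is 0.64.

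n = [1.960·√(2·0.64·0.36) + 0.842·√(0.54·0.46 + 0.74·0.26)]² / 0.20² = (1.330 + 0.559)² / 0.04 ≈ 89.2

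The stated 89 per arm reproduces, so recovery is clearly an intended, sized outcome.

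**2. The places side by side.**

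| Place | Recovery | PHQ-9 score or change |
|---|---|---|
| Implementation, Validation by PRS | not named | collected at all follow-up visits |
| Table 3, Objective 2 | absent | absent |
| Sample size | sized, 89 per arm | absent |
| Table 5 | below 5, no visit | bands only |
| Statistical methods | GEE, no baseline adjustment stated | absent |

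**3. Fall needed to recover.** This is entry score minus 4: 1, 2, 3, 4 and 5 points for entry at 5, 6, 7, 8 and 9. A change from 5 to 4 counts; a change from 9 to 5 (4 points) does not.

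**4. Illustration: no true change.** The documents give no PHQ-9 SD, so noise SDs of 1.5 and 2.5 are assumed, with normal error. For entry score b, P(recovered) = Φ((4.5 − b)/SD).

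| Entry score | SD 1.5 | SD 2.5 |
|---|---|---|
| 5 | 0.369 | 0.421 |
| 6 | 0.159 | 0.274 |
| 7 | 0.048 | 0.159 |
| 8 | 0.010 | 0.081 |
| 9 | 0.001 | 0.036 |
| Even spread over 5–9 (assumed) | 0.117 | 0.194 |

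**5. Illustration: the same improvement for everyone.** Assume a 3-point fall with SD 2. P(recovered) = Φ((4.5 − (b − 3))/2), which gives 89%, 77%, 60%, 40% and 23% for entry at 5 to 9. With an even spread the mean is 58%, near the plan's 54%. One point of entry score moves recovery by 12 to 20 percentage points with an identical treatment effect. The average is (89 − 23)/4 ≈ 17 per point, so half a point between arms in mean entry score would move recovery by about 8 percentage points.

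**6. How different the detected groups might be.** At 5% detection, 1200 × 0.05 = 60 people are detected per arm. If the 20% difference is in percentage points, the other arm detects 1200 × 0.25 = 300. If it is relative, the other arm detects 1200 × 0.06 = 72. These counts cover detected depression as a whole, not only mild cases. On the first reading one arm finds five times as many people, so a different mix of entry scores is plausible. The documents give neither its direction nor its size.

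**7. Information kept by the cut.** For a normal score cut at proportion p, efficiency is φ(z)²/[p(1 − p)]. This is 0.634 at p = 0.54 and 0.547 at p = 0.74. Normality is assumed, and a scale with a floor at 0 may be skewed, so this too is only an illustration.

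**The case against.** The strongest reply is that the definition is coherent. Table 5 uses below 5 for both normal and recovery, so recovery means return to the study's own normal category. Preferring a continuous score is a design choice, and a mixed model for PHQ-9 or a baseline covariate could stand in an analysis plan that is not shown. This is fair as far as it goes: the threshold is not an error, and no change to it is asked for. It does not explain why an outcome that is sized and analysed is absent from the table said to outline the outcomes, why it has no visit, or why scores collected to document change serve no listed outcome.

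A reader might also infer several stronger things that the documents do not support:

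- **That recovery is the only clinical measure of management.** HRQoL is a patient-level outcome under Objective 2 with its own between-arm model. Recovery is the only depression-symptom outcome.
- **That a 1-point fall generally counts as recovery.** This holds only for entry at exactly 5.
- **That recovery mainly reflects noise.** With an even spread of entry scores, the no-change illustration gives 12–19%, well below the assumed 54%. Noise that is alike in both arms dilutes a contrast and does not create one.
- **That the follow-up PHQ-9 is unused.** Recovery is presumably derived from it. What has no stated use is the change and the repeated scores.
- **That the arms will differ in entry score.** They may; nothing in the documents shows that they will.
- **That PHQ-9 score should replace recovery.** Recovery is the outcome that was sized. No SD or target difference for the score is given, so a replacement would have no sample-size basis.

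**Conclusion.** The point holds in this limited form. Three parts rest on the text alone: the required fall runs from 1 to 5 points across the entry band; recovery is sized and analysed but is absent from Table 3 and has no visit; and the PHQ-9 change collected at every follow-up has no stated outcome or analysis. That entry score could distort the recovery comparison follows from the threshold together with a managed group formed after randomisation by unblinded detection.

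The size is illustrative. Under an assumed common 3-point improvement with SD 2, one point of entry score shifts recovery by 12–20 percentage points, against a planned difference of 20. The no-change figures (37–42% for entry at 5, 0.1–4% for entry at 9) and the 55–63% efficiency depend on assumed SDs or normality. The plan should be changed on this point, but the primary detection outcome is untouched.

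**What to change.** - **Table 3, Objective 2:** add recovery (PHQ-9 below 5, as Table 5 defines it), judged from the PRS-administered PHQ-9 at the 11th–12th week visit. It remains the sized management outcome.
- **Statistical methods, recovery:** adjust the GEE comparison for baseline PHQ-9, and say that the PRS score at baseline validation is the one used.
- **Table 3 and Statistical methods, PHQ-9 score:** add the PRS-measured score over the three follow-ups as a supporting Objective 2 outcome. Analyse it with a linear mixed model that accounts for PHC and includes baseline PHQ-9 as a covariate.

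This changes wording in one table and one section and needs no new visits. It assumes that the PRS validation of mild cases records a PHQ-9 score, which the text implies and should state. The costs are one more secondary analysis with no sample-size basis of its own, and possible convergence trouble in a log-link model with a continuous covariate, for which a fallback should be named. Baseline adjustment deals with measured entry score only; other differences in who is detected remain, and the report should say so. The changes are best made before outcome data are examined.
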